## Abstract

**Background:**

Psychological distress is a common occurrence among women during the perinatal period. Maternal psychological distress (MPS) can also have a negative influence on neonatal outcomes such as infant health, child development or mother-child interaction. Hence, interventions to improve mental wellbeing during this period are vital. Mindfulness based intervention (MBI) has been found to be effective in reducing psychological distress. Delivery of MBI via the internet, making it accessible and inexpensive, is showing a promising positive effect in reducing psychological distress. A randomized control trial with sufficient power is required to confirm its positive effect among pregnant women. The positive effects of MBI have been found to be associated with heart rate variability (HRV) biofeedback; however, the efficacy of MBI on HRV has been rarely studied among pregnant women. Also, the potential association of HRV with MBI and psychological wellbeing needs further examination. This research aims to test the effectiveness of guided mobile-based perinatal mindfulness intervention (GMBPMI) among pregnant women experiencing psychological distress during the pre- and post-natal period, as well as examining the efficacy of GMBPMI on HRV.

**Method:**

This study is a randomized controlled trial that follows a parallel design. Consenting pregnant women in their second trimester (between 12^th^ and 20^th^ week gestation) will be randomly assigned to an intervention group (GMBPMI) or a control group (psychoeducation). The intended sample size is 198, with 99 participants in each group. Three levels of outcomes will be measured at baseline, post intervention in both the intervention and control groups, and at 36-week gestation and five-week postpartum. The primary outcomes include maternal psychological stress, mindfulness and positive appraisal HRV. Secondary outcomes are psychological and physical wellbeing. Tertiary outcomes include obstetric and neonatal outcomes, and social support. Analyses will follow an intention-to-treat method and repeated measures MANOVA will be conducted to compare changes in primary and secondary outcomes. A series of mixed-effects models will be fitted to assess the mediation effects.

**Discussion:**

This trial expects to increase understanding of GMBPMI on HRV and psychological wellbeing for pregnant women, with extended support in both pre-and post-natal periods. The study could also potentially provide evidence for delivery of cost-effective and accessible services to pregnant women.

**Trial registration:**

ClinicalTrials.gov: NCT04876014, registered on 30 March 2021. Protocol Version 1.0., 10 May 2021.

## Introduction

Pregnancy, giving birth and becoming a parent are three major life events that happen together. Were it not for the exhilaration of expecting a new life, many women would experience maternal psychological distress due to the naturally occurring physical, emotional and interpersonal changes [1]. MPS refers to the subjective feelings of distress or strain experienced by women during pregnancy [2]. The most common stresses faced by pregnant women include physical health concerns and psychological stress. Physically, they face increased medical and health concerns and physical discomfort during pregnancy. Psychologically, women experience difficulties in navigating a new identity, childbirth-related fear and anxiety, and the pressure of being a ‘perfect mother’ [3–5]. Research has identified many adverse consequences of maternal psychological distress (MPS) related to both mother and child. Some evidence suggests that MPS may be associated with poor obstetric and neonatal outcomes [6–8] including increased maternal obstetric complications such as analgesic use and unplanned caesarean delivery [9, 10]. Furthermore, fetal exposure to MPS can increase the risk of poor neonatal outcomes, including preterm delivery [11], low birth weight [4], low Apgar scores, smaller head circumference and major congenital anomalies [12, 13]. MPS not only affects perinatal maternal and infant health but may also result in poor postpartum mother-child interaction and child development [7, 14]. Recent evidence has also indicated that as well as depression, anxiety during pregnancy is related to developmental and behavioural issues in children [15].

Women in Hong Kong experiences MPS during perinatal period. Mindfulness intervention is increasingly being used to treat symptoms of anxiety, stress and depression [16, 17]. Accumulating evidence has suggested that mindfulness-based intervention (MBI) may be suitable and beneficial for women in coping with physical discomfort and negative emotions or thoughts during the perinatal period [18, 19]. Through mindfulness training, people can increase self-awareness of their emotions, thoughts and sensations, and cultivate curiosity and openness in their experiences without losing themselves in thoughts and feelings. Such skills are considered vital to pregnant women who experience physical discomfort intertwined with their emotions during the perinatal period.

In recent decades, empirical research has suggested the efficacy of MBI in reducing MPS. For example, a meta-analysis of 17 studies of prenatal MBI demonstrated significant pre- and post-improvements of medium effect size in reducing stress and depression [20, 21]. However, there were no significant postnatal improvements in stress and depression or in mindfulness skills for MBI participants versus the control participants [20]. Lau and colleagues [22] suggest a need to implement the intervention in the second trimester and extend the intervention to the third trimester and postnatal to prevent postpartum depression. MBI was also found to be associated with enhanced biological and infant outcomes. Higher maternal mindfulness of women at 22-week gestation significantly predicted a normal, as opposed to low, neonatal birth weight [23]. Van den Heuvel and colleagues [24, 25] showed that maternal mindfulness was negatively correlated with maternal anxiety during pregnancy, and positively associated with fewer infant self-regulation problems, a less difficult temperament, and greater control in infants at ten months old. In a randomized controlled trial examining the efficacy of MBI among pregnant women, Chan [26, 27] found mothers in the MBI group to have lower levels of the “stress hormone” salivary cortisol in the evening, and the infants at five months old had easier temperaments as well as improved positive appraisal. However, the significant effects were only observed among the 56% of participants who practiced mindfulness regularly [28]. Lack of continued motivation was the most common reason reported for giving up the practice, suggesting a need to extend the current MBI from the second trimester of pregnancy to the third trimester and postnatal period.

Previous studies have shown that MBI has led to increased heart rate variability (HRV) as well as decreased blood pressure and cortisol levels [29, 30], suggesting that MBI may have beneficial physiological effects for pregnant women [31]. Most recently, Braeken and colleagues [31] examined 156 pregnant women with self-reported mindfulness, psychological distress and HRV measures. The research highlighted an association between mindfulness and autonomic nerve system (ANS) changes, suggesting that mindfulness improves HRV measures and leads to better social and emotional development in both mother and offspring. However, few randomized controlled trials have been conducted to test the efficacy of MBI on ANS changes in pregnant women.

The present study aims to rigorously evaluate the effectiveness of a guided mobile-based perinatal mindfulness intervention (GMPMI). Specifically, we aim:

to evaluate the effectiveness of GMPMI on psychological distress of women during the perinatal period;to evaluate the impact of GMPMI on obstetric and neonatal outcomes;to investigate HRV changes associated with GMPMI and its mediation effect between maternal psychological distress and neonatal outcomes.

## Method

### Design

The research adopts a parallel-armed, randomized controlled trial (RCT) design. Pregnant women in their second trimester will be recruited through Qualtrics (https://hku.au1.qualtrics.com/jfe/form/SV_2ofenm3v2OeCyJE). Eligible participants will be randomized to receive either the guided mobile-based perinatal mindfulness intervention (GMPMI) or the web-based perinatal psychoeducation program (WPPP). Repeated measures will be taken at four time-points: pre-intervention (T0); on completion of eight weekly PMI in the intervention group or eight weekly PPP on perinatal care in the control group (T1); 36-week gestation (T2); and five-week postpartum (T3).

### Setting

This research is based in Hong Kong. Adopting an online intervention mode, the location of the participants will not compromise their eligibility. The study sites will be the current living environment the participants. The participants will receive perinatal psychoeducation and support, which will be deliberated in the later part.

### Participants

Adult (age 18 or above) pregnant Chinese women in their second trimester (between 12^th^ and 28^th^ week gestation) will be invited to the study. This is when pregnancy becomes stable. Participants will be recruited from the community through advertisements posted on relevant websites, maternal discussion forums, Facebook and Twitter. The exclusion criteria are: 1) not able to understand Chinese (the intervention will be delivered in Chinese); 2) high-risk pregnancy status (e.g., preterm labor, placental abnormality, multiple gestations, required bed rest, or morbid obesity); and 3) current psychiatric disorders necessitating priority attention (e.g., schizoaffective disorder, bipolar disorder or current psychosis; organic mental disorder or pervasive developmental delay; current substance abuse or dependence; imminent suicide or homicide risk).

A screening interview via telephone or audio-chat will be conducted with each potential participant to assess eligibility as well as to explain the study in detail and to address concerns. The eligible participants will receive consent forms by email and will be asked to return these to the researchers.

### Sample size calculation

The previous eastern-based meditation intervention (EBMI) study reported an effect size of 0.44 in reducing prenatal distress and an attrition rate of around 20% [28]. In the proposed study we assume an overall moderate effect size of 0.4 and a conservative attrition rate of 25%. Setting a power at 90%, a significance level of *p* < .008 (corrected for six primary outcomes), a sample size of 99 per arm is needed for a two-arm repeated measures design (GPower, version 3.1). Thus, the targeted total sample size is 198. Considering this is a web-based intervention, we will consider expanding the sample size to ensure enough statistical power after preliminary data analysis.

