### Four hypotheses

The intervention group would show a greater increase in maternal mindfulness and positive appraisal than the control group at T1, T2 and T3.The intervention group would show a greater reduction in stress and depression than the control group at T1, T2 and T3 and these outcomes would be mediated by the enhancement in positive appraisal.The intervention group would show a greater increase in HRV than the control group at T1, T2 and T3 and these outcomes would be mediated by the reduction in stress and depression.The levels of stress and depression would be negatively associated with obstetric and neonatal outcomes at T3 and these correlations would be mediated by HRV.

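### The only multiplicity rule given is single-step Bonferroni at .05/6; if it also serves to judge the primary outcomes, Holm's procedure keeps the same error rate and never rejects less

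*Protocol article*

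**What the plan says.** Sample size calculation (protocol article) sets "a significance level of *p* < .008 (corrected for six primary outcomes", with 90% power and 25% attrition. It adds "we assume an overall moderate effect size of 0.4" and concludes that "a sample size of 99 per arm is needed for a two-arm repeated measures design (GPower, version 3.1". This is the only place where a significance level or a correction for several outcomes appears.

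Data analysis plans a repeated measures MANOVA on the primary and secondary outcomes, with multiple imputation, trend analysis and mixed models. It names neither Bonferroni nor Holm and sets no threshold for the single outcomes.

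Four hypotheses predicts benefit on several primary outcomes together: mindfulness and positive appraisal in the first, HRV in the third, and in the second "The intervention group would show a greater reduction in stress and depression than the control group at T1, T2 and T3".

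**The concern.** A single-step rule holds every outcome to .05/6, even after some of the others have been declared. Holm relaxes the level as outcomes are declared, at the same family-wise error. It gains most when several effects are real at once, which is the pattern that this trial's hypotheses and conceptual framework predict. If .008 is carried into the analysis as the decision rule, the trial accepts lower power for the later outcomes than the same data allow at the same 5% error. At stake is the chance of confirming several outcomes. The chance of finding at least one is hardly affected.

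**Working it through.** **1. The plan's own figures.** 0.05/6 = 0.00833, which agrees with the stated .008. Since 6 × 0.008 = 0.048, the correction holds the family-wise error at or below 5%. The overall .05 is implied by this arithmetic and not written out.

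The 99 per arm can be neither confirmed nor refuted, because the effect-size metric, the type of effect tested and the correlation between repeated measures are not stated. A plain comparison of two means at d = 0.4, two-sided .008 and 90% power needs 2 × (2.652 + 1.282)² / 0.4² ≈ 194 per arm. Some repeated-measures settings come close to the stated figure. For example, an interaction test with f = 0.2, two measurements and correlation 0.25 gives 75 per arm, and 75/0.75 = 100. The working below therefore takes the stated 90% per outcome as an assumption.

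**2. What Holm does.** It compares the ordered p-values with .05/6 = .0083, .05/5 = .0100, .05/4 = .0125, .05/3 = .0167, .05/2 = .0250 and .0500, and stops at the first failure. The first step equals Bonferroni, so Holm rejects everything that Bonferroni rejects.

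**3. Bounds by hand.** A two-sided z-test with 90% power at .05/6 has non-centrality 2.638 + 1.282 = 3.92. Its power at the later levels is Φ(3.92 − z):

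| Level | z | Power |
|---|---|---|
| .0083 | 2.638 | 90.0% |
| .0100 | 2.576 | 91.0% |
| .0125 | 2.498 | 92.3% |
| .0167 | 2.394 | 93.6% |
| .0250 | 2.241 | 95.3% |
| .0500 | 1.960 | 97.5% |

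Average power under Holm must therefore lie between 90% and 97.5%. With three real effects and three nulls, testing will seldom pass beyond .0125, so about 92% is the most to expect.

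**4. Simulation.** Six equicorrelated two-sided z-tests, non-centrality 3.92, 200,000 runs, outcome correlation 0 / .3 / .5 (assumed):

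| Setting | Bonferroni | Holm |
|---|---|---|
| Six real, average power | .90 | .970 / .962 / .956 |
| Six real, all six confirmed | .533 / .621 / .679 | .853 / .868 / .884 |
| Three real, average power | .90 | .921 / .920 / .917 |
| Three real, all three confirmed | .73–.78 | .79–.82 |

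As a check, with independent outcomes Bonferroni should confirm all six with probability 0.9⁶ = .531 and all three with probability 0.9³ = .729.

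A separate run of 100,000 at 194 per arm (d = 0.4, correlation 0 / .3 / .6) covers one real effect: .904 / .903 / .904 under Bonferroni and .904 / .904 / .905 under Holm. The chance of at least one true finding agreed to within 0.1 percentage points in every setting. The family-wise error under Holm stayed below 5% throughout.

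**5. If power is lower than stated.** With d = 0.4, 99 per arm and one post-treatment value, the non-centrality is 0.4 × √(99/2) = 2.81 and power at .05/6 is Φ(2.81 − 2.64) ≈ 57%. Average power under Holm (correlation 0 to .6) is then 67–69% with six real effects, about 60% with three and 57% with one. This ignores both the attrition and the repeated measures.

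**The case against.** A reader might infer that the protocol commits to judging each primary outcome at one fixed level. The text does not say so. The .008 is an input to the sample size, and planning at .05/6 is also what a Holm analysis would do for its first step. The final testing rule may stand in an analysis plan that is not shown. This objection stands, and it is why the point is conditional.

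A reader might also infer that power is being given away for nothing. That goes too far. Bonferroni is valid and widely used, and it yields simple simultaneous confidence intervals. The sample size is stated to give 90% power at the corrected level, so the per-outcome cost is already budgeted.

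The larger gains need all six effects to be real, and the protocol does not make confirmation of all six its criterion of success. The figures also come from univariate z-tests and not from the planned MANOVA. Both reservations stand.

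What the objection does not remove is that .05/6 is the only rule on the page. If it is applied outcome by outcome, another rule with the same error control does at least as well whatever the data.

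**Conclusion.** The plan contains no error on this point. The correction at .05/6 is valid, and nothing in the document contradicts it. The point is a cheap improvement that applies if the same level is used to decide on the primary outcomes.

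On the stated 90% power per outcome, the gain in average power is about 6 to 7 points if all six effects are real, about 2 points if three are, and none of practical size if one is. These sizes rest on assumed correlations of 0 to .5 between outcomes and on univariate tests. That Holm controls the same error and never rejects less than Bonferroni rests on neither assumption.

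**What to change.** Keep .05/k as the level in the sample size statement, where k is the final number of primary outcomes; it is Holm's first step, so the sample size does not change. Add one sentence before unblinding: the per-outcome tests of the k primary outcomes use Holm's step-down procedure at family-wise alpha .05, and adjusted p-values are reported.

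The cost is that one sentence, with no change to data or design. Because simultaneous intervals matching Holm are less simple, show 95% intervals without adjustment and label them as unadjusted. An unadjusted interval can then exclude zero for an outcome that Holm does not declare, and the label should make that clear.

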**Primary outcome variables**		
Maternal psychological stress		
General stress	Perceived Stress Scale –10 items–The scale measures subjective perception of stress with two subscales, perceived helplessness and perceived self-efficacy [36, 37].	T0, T1, T2, T3,
Pregnancy- specific stress	Prenatal Distress Questionnaire– 12 items–The scale consists of three factors–concerns about birth and baby, weight and body image, emotions and relationships [38].	T0, T1, T2
Depression	Edinburgh Postnatal Depression Scale–Chinese– 10 items–The scale has been validated in the Chinese population with satisfactory psychometric properties [39].	T0, T1, T2, T3
Mindfulness		
State mindfulness	Short-form Five Facet Mindfulness Questionnaire– 20 items–The scale consists of five subscales–observing, describing, acting awareness, non-judging of inner experience and non-reacting to inner experience [40].	T0, T1, T2, T3
Daily mindfulness	Daily Mindful Responding Scale– 4 items–A measure designed to assess mindful responding in the daily lives of people undergoing mindfulness training [41].	Every week until T3
Positive appraisal		
Coping	Prenatal Coping Inventory– 22 items–consists of four subscales–preparation, avoidance, positive appraisal and prayer [42].	T0, T1, T2
Heart rate variability		
HRV Index	CorSense by Elite HRV–A merchandise device monitoring heart rate variability	T0, T1, T2, T3

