**Individual factors**		
Socio-demographic	Age, gender, marital status, family income, employment, education, gestational age, parity, obstetric history, medical history, pre-pregnancy BMI.	T0
Social support	Prenatal Social Support– 4 items–The scale measures the level of social support women receive during pregnancy [50].	T0, T1, T2

HRV index will be collected through CorSense device. This device is designed as a finger clip which is portable and easy for the pregnant women to use. HRV scores will be calculated automatically. The higher HRV score indicates a better mental health status. The calculation of HRV score is based on the components of the HRV measurements. The R-R intervals will be captured through the Corsense monitor, followed by an industry standard RMSSD calculation. After applying a natural log (ln) to RMSSD, HRV score is conceptualized with a magnitude ranging from 0 to 100. In the meantime, the Corsense device can also capture the raw data of standard deviation of NN intervals (SSDN), the root mean square of the successive difference (rMSSD) in R-R intervals, and low frequency (LF), high frequency (HF), and very low frequency (VLF). This can serve as complementary data for the research team to do data analysis. Elite HRV provides a Team Dashboard for the research team to manage the participants’ data in a more convenient way. All the HRV scores and raw data will be sent to the Team Dashboard once the participant completed the measurement.

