### Data analysis

Quantitative data including scale measures and the HRV index will be collected at four time-points as articulated above.

Intention-to-treat analysis will be performed and missing data due to drop–out will be handled by the ‘multiple imputation’ technique [51]. 1) Using a two-arm RCT design, the efficacy of the intervention will be examined by repeated measures MANOVA on both the primary and secondary outcome variables, while adjusting for individual factors. Partial eta-squared values will be calculated to measure the effect size; values of .02, .13 and .26 suggest small, medium, and large effect sizes, respectively [52]. 2) To investigate the within-group effect, serial trend analysis from T0 to T3 will be conducted on the primary and secondary outcome variables. 3) A series of linear mixed-effects models will be fitted to assess the mediation effects. 4) The software Elite HRV Team Dashboard will be used for HRV data collection. Three HRV indexes will be computed for analysis, namely RMSSD (Mean squared difference between consecutive normal-to-normal intervals), SDNN (standard deviation of beat-to-beat intervals) and HF (absolute power of HF band).

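### The .008 significance level is corrected for six primary outcomes, but Table 1 lists seven and the status of three HRV indexes is left open, so 5% is no longer guaranteed

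*Protocol article*

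**What the plan says.** All places are in the protocol article.

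- **Sample size calculation.** The threshold is "a significance level of *p* < .008", "corrected for six primary outcomes". It goes with 90% power, an effect size of 0.4, 25% attrition and 99 women per arm.
- **Table 1, primary outcome variables.** Seven measures are listed: Perceived Stress Scale, Prenatal Distress Questionnaire, Edinburgh Postnatal Depression Scale, short-form Five Facet Mindfulness Questionnaire, Daily Mindful Responding Scale, Prenatal Coping Inventory and HRV Index. Six are scheduled at T0 and at later visits up to T2 or T3. The Daily Mindful Responding Scale is taken weekly until T3, with no T0 listed.
- **Measures, HRV paragraph below Table 1.** One score is described: "After applying a natural log (ln) to RMSSD, HRV score is conceptualized with a magnitude ranging from 0 to 100". The raw SDNN, RMSSD and frequency-band values are offered as a supplement to it.
- **Data analysis.** "Three HRV indexes will be computed for analysis, namely RMSSD", SDNN and HF. The text does not say whether these stand beside the score or in its place, or whether any of them is primary. Efficacy is to be tested by repeated measures MANOVA. The .008 level is not restated there.
- **Four hypotheses.** The first three expect group differences at T1, T2 and T3.

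**The concern.** A Bonferroni threshold protects only the set of tests it was computed for. Here the count behind the threshold differs from the count in the protocol's own table, and the HRV outcome has one form in one section and three in another. The abstract, the Measures section and the Discussion speak of four constructs, Table 1 has seven rows, and seven rows with HRV split into three indexes make nine variables. None of these is six.

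Two things are at stake. The stated error control may not cover the tests that are run. And, with the six unnamed, which results count as confirmatory could be settled after the data are seen.

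**Working it through.** **Inputs.** Per-test level .008 and six outcomes (Sample size calculation); seven primary rows (Table 1); three HRV indexes (Data analysis); 99 per arm and 90% power (Sample size calculation). An overall two-sided level of .05 is an assumption. It is not stated, but .05/6 is the usual origin of .008.

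**Step 1: the plan's own figure.** .05/6 = .00833, which prints as .008. Check: 6 × .008 = .048. The threshold does what it says for six tests.

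**Step 2: counting the primary variables.**
- Table 1 as printed: 7.
- Table 1 with the HRV row counted as three indexes: 6 + 3 = 9.
- The same without the weekly mindfulness scale: 5 + 3 = 8.
- Table 1 without the weekly scale and with one HRV variable: 6.

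**Step 3: family-wise error at .008 per test.** The Bonferroni bound is k × .008. Under independence the rate is 1 − (1 − .008)^k. The last three columns are simulated rates with all outcomes equally correlated at r (eight tests were not simulated).

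| Tests k | Bound | Independent | r = .3 | r = .5 | r = .7 |
|---|---|---|---|---|---|
| 6 | 4.8% | 4.7% | 4.5% | 3.9% | 3.2% |
| 7 | 5.6% | 5.5% | 5.1% | 4.6% | 3.5% |
| 8 | 6.4% | 6.2% | – | – | – |
| 9 | 7.2% | 7.0% | 6.4% | 5.6% | 4.2% |

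**Step 4: thresholds that would fit.** Seven: .05/7 = .00714. Nine: .05/9 = .00556.

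**Step 5: cost in power or sample size.** Take the stated 99 per arm as giving 90% power at .008, and use the normal approximation, in which the required n is proportional to (z for alpha/2 + z for power)².
- At .008: 2.652 + 1.282 = 3.934.
- Seven outcomes: z = 2.690. Power at 99 per arm is Φ(3.934 − 2.690) = Φ(1.244) = 89.3%. To keep 90%: 99 × (3.972/3.934)² = 99 × 1.019 = 100.9, so 101 per arm.
- Nine variables: z = 2.773. Power is Φ(3.934 − 2.773) = Φ(1.161) = 87.7%. To keep 90%: 99 × (4.054/3.934)² = 99 × 1.062 = 105.2, so 106 per arm.

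The figure of 99 cannot be reproduced uniquely, because the effect metric, the number of measurements and their correlation are not given. Several settings arrive at 99, so Step 5 scales the stated figure and claims no error in it.

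**The case against.** **A consistent reading exists.** Leave out the one scale that is off the T0–T3 schedule and hold HRV to one index, and Table 1 yields exactly six. The defect may be one unlabelled row. This is plausible, but the article does not say it, and the Data analysis section would still have to say that the three HRV indexes are not each primary. The objection limits the severity; it does not remove the contradiction.

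**The true error rate may be under 5%.** This stands. Psychological scales taken from the same women are likely to be correlated, and at r = .5 seven tests give 4.6%. So the exact statement is that 5% is not guaranteed. A reader might infer that 5% is certainly exceeded; the documents do not support that.

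**Visits need not multiply the tests.** A reader might also infer, from the hypotheses at T1, T2 and T3, a family of 25 tests (3 + 2 + 3 + 3 + 3 + 2, plus 9 for HRV), with an error rate of 1 − .992^25 = 18.2% under independence. That requires separate testing at each visit, which the article does not prescribe. A repeated measures analysis can cover all visits of an outcome in one group-by-time test. The 25 also gives the weekly scale three visits arbitrarily.

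**HRV is not shown to have been replaced.** It is tempting to say that the three indexes supplant the score, so that HRV could succeed on any of four versions. The text says only that they will be computed for analysis, and the Measures section treats the raw values as a supplement. RMSSD and the score are transforms of the same quantity. What stands is that the status of the indexes is unclear.

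**The weekly scale is not shown to be invalid.** Table 1 calls it a "measure designed to assess mindful responding in the daily lives of people undergoing mindfulness training", and a reader might conclude that it cannot compare the arms. That is a statement of purpose. Its behaviour in controls depends on a cited source that is not at hand, and a missing baseline does not invalidate a randomised comparison.

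**This could wait for an analysis plan.** Detailed contrasts can. But the article itself fixes a count and a threshold, and its own table disagrees with that count.

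**Conclusion.** The point holds in a limited form and should be fixed, though it does not threaten the design. The threshold is tied to six primary outcomes, Table 1 shows seven, the six are not named, and the role of three HRV indexes is undefined. The bound on family-wise error rises from 4.8% to 5.6% for seven or 7.2% for nine. With strong correlation the true rate may lie below 5% even for nine (4.2% at r = .7).

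This assumes an overall two-sided level of .05, use of .008 as the decision level for each primary outcome, and one test per outcome across its visits. The correlated figures assume equal correlation between all outcomes; the actual correlations are not given.

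**What to change.** Make the primary list and the threshold agree, in one of two ways.

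1. **Keep .008 and name exactly six primary variables.** For example, make the weekly Daily Mindful Responding Scale a process measure, name the ln-RMSSD score as the single HRV primary, and make SDNN and HF secondary. State one test per primary variable across its own scheduled visits. Cost: one scale and two HRV indexes have no primary status. The threshold and the 198 women stay as they are.
2. **Keep all variables and restate the threshold** as .05/7 (.0071) or .05/9 (.0056). For nine, write the fraction or .0055, because 9 × .0056 = .0504. Restate power at 99 per arm as about 89% or 88%, or raise the target to about 101 or 106 per arm.

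Either way, repeat the threshold in the Data analysis section and state there whether RMSSD, SDNN and HF are primary or secondary. Whichever option is chosen, it should be recorded before outcome data are analysed.
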